Considering the complexity of large alveolar clefts and the limitations of conventional bone grafting, this study aims to evaluate the outcomes of dentoalveolar transport distraction compared with unilateral Le Fort I advancement. The analysis will focus on cleft gap closure, maxillary arch form, the stability of mobilized section, and postoperative healing. This comparative assessment will offer sought-after information to direct surgical decision-making in the treatment of wide alveolar clefts, as the traditional techniques often fail due to graft resorption, soft tissue dehiscence, or inadequate bone regeneration.

While both unilateral Le Fort I advancement and dentoalveolar transport distraction have been independently used for managing large alveolar clefts, comparative clinical data between these 2 techniques are lacking. Current literature focuses on individual case series or retrospective studies, with no consensus on which method yields superior outcomes in terms of bone regeneration, stability, or soft tissue healing. Given the unpredictability and donor site morbidity of traditional grafting methods in wide clefts, a direct prospective comparison of these 2 graftless techniques is warranted. This study aims to fill that gap by systematically evaluating and comparing the clinical, esthetic, and radiographic outcomes of both procedures in patients with large alveolar clefts.

To guide the comparison between unilateral Le Fort I advancement and dentoalveolar transport distraction in the management of large alveolar clefts, the following hypotheses were formulated:

Alternate hypothesis—there is a detectable difference between unilateral Le Fort I advancement and dentoalveolar transport distraction in at least 1 of the following outcomes: alveolar gap closure (measured radiographically), arch form (classified clinically and radiographically), stability of the mobilized segment (graded on the bone stability scale), or soft tissue healing (graded on the Landry wound healing scale) in patients with large alveolar clefts.Null hypothesis—there is no detectable difference between unilateral Le Fort I advancement and dentoalveolar transport distraction in alveolar gap closure, arch form, segment stability, or soft tissue healing outcomes in patients with large alveolar clefts.

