### Sample Size Calculation

The minimum required sample size was calculated using the standard formula for comparing 2 independent means, as shown below:

$$N=\frac{{\left(Z_{\alpha }+Z_{\beta }\right)}^{2}\left(P_{1}\left(1-P_{1}\right)+P_{2}\left(1-P_{2}\right)\;\right)}{{\left(P2-P1\right)}^{2}}$$

$$Z_{\alpha }=1.64$$

α= Type I error at 5%

$$Z_{\beta }=0.84$$

β= Type II error at 20%

The following parameters were used for the sample size calculation:

Improved facial esthetic and balance in maxillary DO=94%Improved facial esthetic and balance in maxillary unilateral Le Fort 1 osteotomy=44% (estimated clinically significant difference=50%)Difference (P2−P1)=50%Minimum sample size N=2×(1.64+0.84)^2^ (0.94) (1‐0.94) + 0.44(1‐0.44)/(0.50)^2^=7 each in 2 groupsSample size=14, with 7 in each group

Using a 2-sided z test with *α*=.05 and power of 80%, assuming a success rate of 94% in the dentoalveolar transport distraction group and 44% in the unilateral Le Fort I advancement group, the required sample size is 7 per group (N=14). This includes a 50% absolute effect size and accounts for variability in response.

The 50% effect size estimate was based on the internal pilot data and clinical observations. However, we acknowledge the possibility of overestimation. A sensitivity analysis will also consider a 40% effect size, which would require a larger sample and will be addressed in future studies.

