## Discussion

### Anticipated Findings

This prospective observational study compares 2 graftless surgical techniques—unilateral Le Fort I advancement and dentoalveolar transport distraction—for the management of large alveolar clefts. On the basis of prior evidence, we anticipate that dentoalveolar transport distraction may achieve more predictable closure of wide alveolar gaps due to its capability for simultaneous bone and soft tissue regeneration through gradual mechanical tension [8,9]. Unilateral Le Fort I advancement, while traditionally used for midfacial hypoplasia and skeletal advancement, may offer improved esthetic facial projection but may be limited by the extent of cleft closure, particularly in large defects [10]. This study will evaluate and compare the clinical, radiographic, and soft tissue healing outcomes of both interventions to identify their respective advantages.

Several studies have demonstrated the effectiveness of dentoalveolar transport distraction in achieving successful cleft closure, even in patients for whom conventional bone grafting had failed [8,9,12]. These techniques exploit the principle of DO, first introduced to the craniofacial skeleton by McCarthy et al [7] and later adapted to the alveolar ridge [8]. Similarly, Le Fort I osteotomy, first described for cleft-related maxillary retrusion, has shown good results in terms of facial profile improvement and occlusion correction [11]. However, few prospective studies have evaluated these 2 methods head-to-head in a controlled population with similar cleft widths, making direct clinical comparison difficult. This study aims to address this gap by applying standardized clinical and radiographic outcome measures across both groups.

The study’s strengths include its prospective design, structured follow-up, and the use of objective evaluation tools, including CBCT for gap measurements and standardized scales such as the Landry wound healing scale and the bone stability scale. By focusing on large clefts (≥1 cm) and excluding patients with bilateral defects or prior interventions, the study enhances internal validity. Limitations include the relatively small sample size, which may limit generalizability, and the nonrandom allocation of patients to treatment groups based on clinical feasibility. However, multivariate regression will be used to adjust for baseline differences, and standardized surgical and postoperative protocols will minimize procedural variability.

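### The sample size of 7 per group uses a one-sided constant and rounds 7.45 down, but is reported as a two-sided 5% test with 80% power; the same formula gives about 67%

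*Protocol article*

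**What the plan says.** The Sample Size Calculation section of the protocol article displays the usual per-group formula for two proportions with unpooled variance. It sets Z_alpha to 1.64, beside "α= Type I error at 5"% with no sidedness given, and Z_beta to 0.84 for a type II error of 20%. The rates are 94% for distraction and 44% for Le Fort I, a difference of 50 points. The worked line begins "Minimum sample size N=2×(1.64+0.84)^2" and ends at 7 in each of two groups.

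The next paragraph describes the same result as "Using a 2-sided z test with *α*=.05 and power of 80"%, and concludes that "the required sample size is 7 per group (N=14"). The section admits that the 50-point effect may be too large, and says of a 40-point effect that it is one "which would require a larger sample and will be addressed in future studies".

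The alternate hypothesis in the Introduction has no direction: "there is a detectable difference between unilateral Le Fort I advancement and dentoalveolar transport distraction" in at least one of four outcomes. The Statistical Analysis section uses P<.05 and does not mention one-sided testing.

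**The concern.** A two-sided test at 5% uses 1.96; 1.64 belongs to a one-sided test at 5%. The section uses the second and names the first, so the constant and the description cannot both be right. Separately, a minimum sample size that comes out at 7.45 has to be rounded up.

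This calculation is the only support given for N=14. If the power is overstated, a non-significant comparison would be read as if the design had an 80% chance of detecting a 50-point difference, when its own formula does not give that. The article hopes to inform treatment guidelines, so a null result could be taken for evidence that the techniques are alike.

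**Working it through.** **Inputs** (all from Sample Size Calculation): P1 = 0.94, P2 = 0.44, difference 0.50, Z_alpha = 1.64, Z_beta = 0.84, equal groups. The only value brought in is 1.96, the two-sided 5% normal quantile.

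**Formula as displayed:** n per group = (Z_alpha + Z_beta)² × v / (P2 − P1)², with v = P1(1 − P1) + P2(1 − P2).

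v = 0.94 × 0.06 + 0.44 × 0.56 = 0.0564 + 0.2464 = 0.3028.

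**1. The plan's own figure.** (1.64 + 0.84)² × 0.3028 / 0.25 = 6.1504 × 0.3028 / 0.25 = 7.45. This gives 7 only if rounded down; rounded up it is 8.

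**2. The test that the text names.** (1.96 + 0.84)² × 0.3028 / 0.25 = 7.84 × 0.3028 / 0.25 = 9.50, so 10 per group and 20 in total.

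**3. Power at 7 per group, same formula.** Power = Φ(√(n × 0.25 / v) − Z_alpha). At n = 7, √(1.75 / 0.3028) = 2.404.
- With 1.64: Φ(0.764) = 78%.
- With 1.96: Φ(0.444) = 67%.

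At 10 per group the two-sided power is 82%.

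**4. How far the approximation can be trusted.** At 7 per group and a 94% rate, the expected number of failures in the distraction group is 7 × 0.06 = 0.42, which is too few for a normal approximation. Other two-sided methods for 94% against 44%:

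| Method | Power at 7 per group | n per group for 80% |
|---|---|---|
| Unpooled z (the plan's formula) | 67% | 10 |
| Arcsine | 61% | 11 |
| Pooled z | 53% | 13 |
| Fisher exact | 25% | about 15 |

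Fisher exact power is 52% at 10 per group, 79% at 14 and 80% at 15. None of these methods gives 7, and the plan's formula is the most favourable of them.

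**5. Notation.** The worked line carries a leading factor 2 that the displayed formula lacks. With the intended brackets it gives 2 × 7.45 = 14.9, which makes sense only as a total. Taken literally without brackets it gives 2 × 6.1504 × 0.0564 + 0.2464 / 0.25 = 1.68. The section also introduces the formula as one for comparing means, although it compares proportions. None of this lowers N.

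**6. The 40-point case, two-sided.** The section does not say which rate moves, so both options are shown.
- 94% against 54%: v = 0.0564 + 0.2484 = 0.3048; n = 7.84 × 0.3048 / 0.16 = 14.94, so 15 per group; power at 7 is 48%.
- 84% against 44%: v = 0.1344 + 0.2464 = 0.3808; n = 7.84 × 0.3808 / 0.16 = 18.66, so 19 per group; power at 7 is 40%.

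**The case against.** The strongest reply is that nothing in the conduct of the study changes. It is a small non-randomised study with 12 of 14 patients enrolled, and small size is already a stated limitation. That is true, and it limits the remedy to a correction of text; it does not make the power statement right. A one-sided intention would not rescue it either: the section says two-sided, and one-sided still requires 8.

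A second reply is that 10 per group and 67% are themselves poor guides. This stands. Statistical Analysis names chi-square or Fisher exact for categorical outcomes, and the exact figures are much worse. The corrected text should say so. Moreover, the 94% and 44% are rates of improved facial esthetics and balance, whereas the listed primary outcomes are gap closure and arch form. The 67% therefore describes the calculation as written, not the power for those outcomes.

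Four stronger readings are tempting, but the document does not support them:
- *The factor 2 shrank the sample.* It did not: 14.9 is just twice 7.45. Only the constant and the rounding lower N.
- *Power is really 55%.* The same formula gives that for 7 against 5, but this split is enrolment as of June 2025 with recruitment still open. The planned split is 7 and 7.
- *The Discussion contradicts the assumed direction.* It says Le Fort I "may offer improved esthetic facial projection but may be limited by the extent of cleft closure". That is hedged and does not claim an esthetic result better than distraction. The argument is also unnecessary, since the section itself says two-sided.
- *Deferring the 40-point case is an error.* The section openly says that a larger sample would be needed. Deferral is unhelpful, but it is not an arithmetic mistake.

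**Conclusion.** The stated size and power are wrong as written, and nothing elsewhere in the article cures the mismatch. For 94% against 44%, the displayed formula requires 8 per group with the constant used and 10 per group with the two-sided constant that the text implies. At 7 per group, two-sided power is about 67% instead of 80%, so the chance of missing the assumed difference is about 33% instead of 20%.

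These figures rest on the plan's assumed rates, equal groups and the unpooled normal approximation. The approximation flatters the design, so 67% is best read as an upper figure; two-sided Fisher exact power is about 25%. The constant and the rounding cause the shortfall. The factor 2, the missing brackets and the reference to means are notation defects.

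**What to change.** Keep N=14 and correct the Sample Size Calculation section:
- Replace 1.64 with 1.96 and round up.
- Make the worked line match the displayed formula (remove the factor 2, add the brackets), and label it as a comparison of two proportions.
- State that for 94% against 44% the formula requires 10 per group for 80% power, so that the planned 7 per group gives at most about 67%.
- Add that both figures are normal approximations that are optimistic at this size: two-sided Fisher exact power is about 25% at 7 per group, and about 15 per group are needed for 80%.
- Optionally, report the 40-point case now from the same formula, saying which rate is assumed to move: 15 per group and 48% power at 7 (94% against 54%), or 19 per group and 40% (84% against 44%).

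The cost is the rewording of one section and a less favourable power statement. No patient, outcome or analysis changes.

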### Primary Outcome

The primary outcomes evaluated in this study will be as follows:

Closure of the alveolar gap: measured clinically and radiographically (ie, CBCT) at 5 time points: preoperatively; immediately after surgery; and at 1, 3, and 6 months and 1 year of follow-upArch form: classified (U-shaped, V-shaped, or asymmetrical) via models and radiographs at each follow-up

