## Methods

### Overview

This is a nonrandomized, prospective observational study conducted at the Department of Oral and Maxillofacial Surgery, Siddharth Gupta Memorial Cancer Hospital, in collaboration with Sharad Pawar Dental College, Maharashtra, India. The estimated study duration is from April 2023 to December 2025.

A total of 17 patients have been screened, of whom 70.58% (12/17) participants have met the eligibility criteria and have been enrolled. Patients have been allocated to 1 of 2 intervention groups (dentoalveolar transport distraction or unilateral Le Fort I advancement) based on individualized clinical considerations, including cleft morphology, available bone stock, and expected compliance with the treatment protocol. Allocation was determined by the treating maxillofacial surgeon in accordance with predefined feasibility criteria.

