### Outcome Measures and Data Collection

Data collection will occur at predefined intervals: preoperatively; immediately after surgery; and at 1, 3, 6, and 12 months of follow-up.

The following outcome variables will be systematically evaluated in both groups:

Alveolar gap closure will be measured radiographically using cone beam computed tomography (CBCT) at each interval.Maxillary arch form will be classified (U-shaped, V-shaped, or asymmetrical) using dental models and occlusal views.Segment stability will be assessed clinically and via CBCT using the 5-point bone stability scale.Soft tissue healing will be evaluated by blinded assessors using the Landry wound healing scale.

All CBCT images will be anonymized and randomized. Two independent evaluators, blinded to group assignment, will perform measurements. If visible hardware reveals the treatment allocation, a second reviewer re-evaluated the image independently.

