### Preoperative Assessment

All patients will undergo clinical examination and medical history review. Informed consent will be obtained. The interdental cleft width will be measured using Castroviejo calipers, and arch form will be classified. CBCT, lateral cephalograms, and maxillary occlusal radiographs will be performed to assess the cleft.

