### Postoperative Care

All patients will receive antibiotics, analgesics, chlorhexidine mouth rinses, and dietary instructions. Follow-up visits will be scheduled at 1 month, 3 months, 6 months, and 1 year postoperatively.

As this is a prospective observational study, treatment allocation is not randomized. Patients are assigned to either the dentoalveolar transport distraction group or the unilateral Le Fort I advancement group based on specific clinical indications determined by the treating maxillofacial surgeon. Criteria such as cleft morphology, cleft width, presence of adequate bone stock for distraction, soft tissue quality, and anticipated compliance with the distraction protocols are considered during group assignment. To minimize selection bias, all assessments are conducted using standardized protocols, and outcome evaluators are blinded to the intervention type. Additionally, baseline characteristics of both groups will be statistically compared to assess equivalency, and any confounders will be adjusted for during analysis using multivariate regression techniques.

To further minimize allocation bias inherent to the nonrandomized design, we will perform stratified enrollment based on cleft width and age groups. Additionally, a propensity score adjustment will be conducted in the final analysis to balance any observed confounders between groups.

Missing data may arise from loss to follow-up or incomplete clinical or radiographic records. These will be assessed for randomness using the Little missing completely at random test. If data are missing at random, multiple imputation using chained equations will be applied to minimize bias. Variables with >20% missing data will be excluded from the primary analysis but may be used in sensitivity analysis. Potential confounders, such as patient age, cleft width at baseline, and compliance with treatment protocols, will be identified a priori based on clinical relevance and literature review. These variables will be included in multivariate regression models (eg, linear regression for continuous outcomes such as gap width and logistic regression for binary outcomes such as successful closure) to adjust the primary effect estimates. Adjusted effect sizes and CIs will be reported alongside unadjusted comparisons.

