### Statistical Analysis

All data will be analyzed using RStudio (version 4.3.2; Posit, PBC). Continuous variables (eg, cleft width and bone segment stability score) will be tested for normality using the Shapiro-Wilk test. Depending on data distribution, between-group comparisons will be performed using either the unpaired *t* test (for normally distributed data) or the Mann-Whitney *U* test (for nonparametric data). Categorical outcomes, such as arch form classification (U-shaped, V-shaped, or asymmetrical) and wound healing grades (from the Landry wound healing scale), will be compared using the chi-square test or Fisher exact test, as appropriate.

Longitudinal outcomes (eg, segment stability across time points) will be analyzed using repeated measures ANOVA for normally distributed data or generalized estimating equations for nonparametric repeated measures. All outcome measures will be reported with 95% CIs, and *P*<.05 will be considered statistically significant. Missing data will be handled using multiple imputation, and any potential confounders, such as age or initial cleft width, will be adjusted for using multivariate regression analysis.

To assess the robustness of results, sensitivity analysis will be conducted by comparing results from multiple imputation with complete-case analysis and worst-case scenario imputation.

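### The only test named for arch form, a primary outcome, leaves out the recorded preoperative class, and the general confounder adjustment does not clearly bring it in

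*Protocol article*

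**What the plan says.** All references are to the Protocol article.

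- **Outcome.** Primary Outcome lists two primary outcomes. The second is arch form, "classified (U-shaped, V-shaped, or asymmetrical) via models and radiographs at each follow-up". The entry for gap closure names a preoperative time point; the entry for arch form does not.
- **Baseline.** Preoperative Assessment states: "The interdental cleft width will be measured using Castroviejo calipers, and arch form will be classified". Outcome Measures and Data Collection agrees: "Data collection will occur at predefined intervals: preoperatively; immediately after surgery; and at 1, 3, 6, and 12 months of follow-up". The preoperative class will therefore be on file.
- **Allocation.** Overview says that patients were assigned "based on individualized clinical considerations, including cleft morphology, available bone stock, and expected compliance with the treatment protocol". Postoperative Care repeats this with a longer list: "Criteria such as cleft morphology, cleft width, presence of adequate bone stock for distraction, soft tissue quality, and anticipated compliance".
- **Test.** Statistical Analysis groups "Categorical outcomes, such as arch form classification (U-shaped, V-shaped, or asymmetrical) and wound healing grades" and assigns them a chi-square or Fisher exact test. It gives no baseline term, no definition of change and no time point for arch form.
- **Adjustment.** Postoperative Care plans a comparison of baseline characteristics, multivariate regression for confounders in general and a propensity score. Adjusted and unadjusted results are to be shown together. The examples it names are: "Potential confounders, such as patient age, cleft width at baseline, and compliance with treatment protocols, will be identified a priori". Enrollment is to be stratified by cleft width and age. The models given as examples are linear for continuous and logistic for binary outcomes.

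**The concern.** In a nonrandomized comparison, the preoperative value of the outcome is usually the first covariate to account for. Here the surgeon chooses the operation partly from the shape of the cleft, and the outcome is the shape of the arch. If one group starts with more U-shaped arches, it will tend to finish with more, even when the two operations do the same to arch form. A chi-square or Fisher test on the class cannot separate that head start from a treatment effect. Arch form is one of only two primary outcomes, so a biased estimate would feed directly into the study's main conclusion about which technique to prefer.

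**Working it through.** **1. Does any stated element use preoperative arch form?**

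| Element | What is named | Preoperative arch form named? |
|---|---|---|
| Test for arch form (Statistical Analysis) | chi-square or Fisher exact | no |
| Confounder examples (Postoperative Care) | age, baseline cleft width, compliance | no |
| Confounder examples (Statistical Analysis) | age, initial cleft width | no |
| Enrollment strata (Postoperative Care) | cleft width, age | no |
| Propensity score (Postoperative Care) | observed confounders, not listed | possible |
| Regression (Postoperative Care) | confounders in general; linear or logistic as examples | possible, but neither model directly fits three unordered classes |

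**2. How large could the bias be?** The document gives no preoperative arch-form distribution, so every share below is an assumption. To keep the sum simple, arch form is reduced to U-shaped or not; the planned test would use three classes. The group size is the planned 7 vs 7 (Sample Size Calculation) and the criterion is P<.05 (Statistical Analysis).

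The rejection probability is the sum of Bin(a; 7, pA) × Bin(b; 7, pB) over all pairs (a, b) whose two-sided Fisher P is below .05. At 7 vs 7 these pairs are 0 against 5 or more, 1 against 6 or more, and 2 against 7, in either direction.

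*Scenario A: neither operation changes the class, so the true effect is nil.*

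| Preoperative U-shaped | False difference | Fisher rejects |
|---|---|---|
| 30% vs 30% | 0 points | 0.7% |
| 60% vs 40% | 20 points | 4.0% |
| 60% vs 20% | 40 points | 15.4% |
| 80% vs 20% | 60 points | 44.8% |

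At the enrollment reported in Results (7 vs 5), 60% vs 20% gives 15% to 19%, depending on which group has the higher share, and 80% vs 20% gives 41%.

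*Scenario B: both operations turn half of the non-U arches into U-shaped ones, and U-shaped arches stay so.* The postoperative share is p + (1 − p) × 0.5.

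- Start at 60%: 0.60 + 0.40 × 0.5 = 0.80.
- Start at 20%: 0.20 + 0.80 × 0.5 = 0.60.
- The false difference is 20 points, and Fisher rejects in 2.8% of studies at 7 vs 7.

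In B the estimate is biased, yet a false positive is rarer than the nominal 5%.

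**3. Which repair removes the bias?** Take scenario B with a 60% vs 20% start.

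- *Share improved among all patients:* 0.40 × 0.5 = 20% vs 0.80 × 0.5 = 40%. This is a false 20-point difference in the opposite direction, because a patient who is already U-shaped cannot improve.
- *Share that became U-shaped among those not U-shaped before surgery:* 50% vs 50%. The bias is gone.
- *Price of the second measure:* the expected number at risk is 7 × 0.4 = 2.8 vs 7 × 0.8 = 5.6, or about 3 vs 6. With an 80% vs 20% start it is 1.4 vs 5.6, or about 1 vs 6. At 1 vs 6 the smallest attainable two-sided Fisher P is 1/7 = 0.14, so no result could be significant.

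**The case against.** The strongest reply is that Postoperative Care already answers the point. It promises a baseline comparison, regression for whatever confounders arise, a propensity score for those observed, and adjusted results next to unadjusted ones. The confounder list is introduced as examples, preoperative arch form is an observed variable, and a propensity score needs no model for a three-class outcome. Secondary Objectives also puts change over time within each group in scope. An article may leave its full covariate list to a longer plan.

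Much of this stands. A reader might infer that arch form will be compared on the postoperative class alone. The document does not support that: the chi-square or Fisher test is the only test named for it, but not the only analysis promised. A reader might also infer from the 15% and 45% figures that a false positive is likely. That is not supported either. They need a large imbalance and no change in class, and the document says nothing about the imbalance. Nor does it say that cleft morphology, as used in allocation, tracks arch class; that link is plausible but inferred.

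What does not fall away is that the article itself fixes a test without a baseline term and names confounders, strata and example models, none of which provides for the preoperative value of this primary outcome. With 14 patients, a regression on several covariates plus a propensity score would also be weak protection, even if arch form were among the covariates. The within-group objective describes each group over time; it does not adjust the comparison between groups.

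**Conclusion.** The point holds in a limited form. The named analysis of a primary outcome does not use its recorded preoperative value, in a study where surgeons allocate partly on cleft morphology. The general adjustment could cover the gap but is not specified to do so. The consequence is possible bias in the arch-form estimate, of unknown size and direction. Under assumed preoperative shares of 60% vs 20% the false difference is 40 points if no class changes (about 15% of studies reject at 7 vs 7). It is 20 points if half of the non-U arches convert in both groups (2.8% reject). Both figures rest on those assumed shares, on a two-class simplification and on equal effects of the two operations. The risk lies more in the reported estimate and its interval than in the P value. The change is worth making because the data are already being collected.

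**What to change.** Before outcomes are compared between groups:

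1. Show the cross-table of preoperative by 12-month arch form for each group.
2. Add preoperative arch form to the named confounders in Postoperative Care.
3. In Statistical Analysis, compare 12-month arch form conditional on the preoperative class. Use either an exact test stratified by preoperative class, or the proportion that became U-shaped among patients who were not U-shaped before surgery. Choose one and state it.
4. Do not compare improved, unchanged and worse across all patients. Patients already U-shaped cannot improve, and the scale would need a ranking of V-shaped against asymmetrical that the protocol does not define.

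**Cost.** No new data and no regression model are required. The downside is precision: if many patients are U-shaped before surgery, few remain informative, and at about 1 vs 6 at risk significance is out of reach. The arch-form result should therefore be read mainly as an estimate with its 95% CI, with the cross-table beside it.
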